#### Security set (SS)

The SS included all actual cases that have received at least one feeding tube placement after randomization, with the safety endpoints recorded. The incidence of adverse events is denominated by the number of patients in the safety set.

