#### Endoscopic feeding tube placement

A nasogastric feeding tube is inserted by nursing staff for the control group. Currently, in our clinical practice, the postpyloric feeding tube can be established by self-propelled dynamics from the gut with the assistance of prokinetic agents [34–36] and using a rescued bedside tube placement method by ICU physicians when necessary [37]. However, despite the short learning curve [38] and easy availability of the methods mentioned above, especially in the advantage of some decision support tools [39, 40], we otherwise decided to employ the endoscopic approach to establish the postpyloric feeding tube promptly and reliably for the study group. Hence, experienced endoscopists must be equipped when participating centers are recruited. In most ICUs currently in China, no special endoscopists are regularly prepared. In this case, a training course on endoscopic postpyloric tube placement is established to equip the physicians to become experienced endoscopists in the ICU.

Detailed training protocol is attached as Supplementary Appendix 4 in this manuscript. The essential procedures of endoscopic tube placement are as follows:

Patients are provided with oxygen inhalation, and ECG and blood oxygen saturation are monitored. After the patient is narcotized, they take the left lying position. During the operation, no secretion could be left in the mouth. A lubricated nasointestinal tube, approximately 25cm deep, is inserted through the nostrils and sent to the gastric lumen by gastroscopy. The esophagus, stomach, and duodenum are observed to confirm the absence of lesions or obstruction. The head end of the nasointestinal tube is clamped with foreign body forceps, and it is slowly pushed into the descending part of the duodenum to fix the nasointestinal tube. The gastroscope is returned to the gastric cavity, and the foreign body forceps are released into the gastric cavity. After about three times, they are transported to about 20–40 cm below the Treitz ligament. After the nasointestinal tube is fixed, the gastroscope and the nasointestinal tube guidewire are withdrawn.

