#### Safety endpoints

The safety outcomes are major adverse tube-associated events (MATEs), including vital sign alert events (defined as HR, RR, or MAP fluctuating beyond the range of ± 15%, or pulse oxygen saturation declining to < 90%), the requirement for sedatives or analgesics during tube placement, vomiting, rhinorrhagia, misplacing into the thoracic cavity, gastrointestinal bleeding or perforation, and so forth.

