#### Per protocol set (PPS)

PPS refers to all participants who fulfill the eligibility criteria and achieve gastric or postpyloric tube placement per randomization. They have good compliance with the trial protocol, such as being ready to receive treatment and measurement for the primary efficacy endpoints, with the required contents in the CRF filled. PPS is used to analyze the primary efficacy endpoints.

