#### Data analysis

All analyses will be performed according to the ITT principle. A *P* value < 0.05 is considered statistically significant. All tests are two-sided with no adjustment for multiple comparisons. Continuous variables are reported as means and standard deviations or medians and interquartile ranges. Categorical variables are reported as proportions. Pearson’s chi-squared test and adjusted multivariable analysis will be applied for the primary outcome. We plan to perform subgroup analyses for the primary outcome for predefined variables: the proportion of patients with at least 1 VAP episode. All the other data, including age, gender, body mass index (weight, height), SOFA score, primary admission diagnosis, coexisting illness, and type of admission, will be presented as descriptive results. Pearson’s chi-squared test will compare incidence or mortality outcomes between groups. The *t*-test will compare total VAP episodes, SOFA scores, time to VAP onset from mechanical ventilation, mechanical ventilation duration, ICU and hospital lengths of stay, inflammatory biomarkers, and function indicators between groups. A paired *t*-test or repeated measures ANOVA will be used to compare baseline and changes during the intervention.

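### The safety set requires a tube placement received and safety endpoints recorded, so harm from aborted or unrecorded placements can drop out of the adverse-event rates, with more opportunity for this in the postpyloric arm

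*Protocol article*

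**What the plan says.** The section Security set (SS) sets two conditions for entry: "The SS included all actual cases that have received at least one feeding tube placement after randomization, with the safety endpoints recorded". The next sentence fixes its use: "The incidence of adverse events is denominated by the number of patients in the safety set".

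The safety outcomes are major adverse tube-associated events (MATEs). Besides vital-sign alerts and desaturation, the section Safety endpoints lists "the requirement for sedatives or analgesics during tube placement, vomiting, rhinorrhagia, misplacing into the thoracic cavity, gastrointestinal bleeding or perforation, and so forth". Safety of PTF is one of the two primary objectives.

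The arms undergo different procedures. Nursing staff insert the control tube. For PTF the protocol says "we otherwise decided to employ the endoscopic approach to establish the postpyloric feeding tube promptly and reliably for the study group". The patient is narcotized and scoped, and the procedure includes a check: "The esophagus, stomach, and duodenum are observed to confirm the absence of lesions or obstruction".

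Two other statements bear on the denominator. The section Analyses set acknowledges randomised patients in whom no tube was inserted, because of illness severity or the physician's decision, and keeps them in the analyses. The section Data analysis says "All analyses will be performed according to the ITT principle".

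**The concern.** A safety denominator should be fixed by exposure to the risk, not by how the exposure ended. Here the risk begins with sedation and with introduction of the endoscope or tube. The set is defined later, by whether a placement was received and whether safety endpoints were recorded. Desaturation, bleeding or perforation can occur during an attempt and can also be the reason it stops. If such a patient never gets a tube, the event may be lost together with the patient.

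The opportunity for this is unequal, because only PTF involves planned narcosis and endoscopy. Exclusions therefore need not balance between the arms, and the comparison affected serves a primary objective.

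**Working it through.** **Which patients leave the set**

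1. *Attempt aborted, no tube ever placed.* This depends on what placement means. The section Intention-to-treat set keeps patients whether or not they received a nasogastric tube placement; there the phrase describes getting the treatment, which supports reading it as a tube placed. On the other side, the PPS asks that patients "achieve gastric or postpyloric tube placement per randomization". That verb is stronger than *received*, and misplacement is itself a MATE, so placement can also mean the procedure. The text does not settle it.
2. *Attempt aborted, rescue tube placed.* The patient has had at least one placement and stays in. The arm for analysis is not stated. If patients are analysed as treated, an event caused by the PTF procedure could be counted under gastric feeding (GTF).
3. *Death or withdrawal before safety endpoints are recorded.* The patient leaves on either reading of placement. Table 2 schedules MATE evaluation only on D1 and D2, so a very early death or withdrawal could lack that record.
4. *Death with safety data recorded.* The patient stays in.

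**Conflict between sections**

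The section Analyses set keeps patients without a tube, and Data analysis puts all analyses under intention to treat. On the tube-placed reading, the SS removes those same patients from adverse-event incidence. No sentence says which rule governs safety.

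**Size**

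The plan gives no figure to reproduce on this point. The only documented input is the arm size, 924 / 2 = 462 at 1:1 allocation. The rest is assumed:

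- f = share of PTF patients excluded from the SS, taken as 5% (0.05 × 462 ≈ 23 patients) or 10% (0.10 × 462 ≈ 46)
- r = event rate among those included, 10%
- a = event rate among those excluded, 0% to 100%

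Rate over all attempted = (1 − f) × r + f × a. The SS reports r, so its error is r − [(1 − f) × r + f × a] = f × (r − a).

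With f = 5%, r = 10%:

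| a | Rate over all attempted | SS reports | Error (points) |
|---|---|---|---|
| 0% | 0.95 × 10% + 0.05 × 0% = 9.5% | 10% | +0.5 |
| 10% | 9.5% + 0.5% = 10.0% | 10% | 0 |
| 50% | 9.5% + 2.5% = 12.0% | 10% | −2.0 |
| 100% | 9.5% + 5.0% = 14.5% | 10% | −4.5 |

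With f = 10%, the rate over all attempted runs from 9.0% (a = 0%) to 19.0% (a = 100%), so the error runs from +1.0 to −9.0 points.

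The sign is that of r − a. Harm is understated only if excluded patients had more events than included ones.

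**The case against.** The best case for the plan is that placement already means the procedure. The section describing it is headed as endoscopic tube placement, the safety endpoints speak of events during placement, and only the PPS demands success. On that reading attempted placements are in the set. Even on the strict reading, the described sequence sends the tube to the gastric lumen before the check for lesions, and a patient later given any feeding tube stays in. A recorded perforation is a recorded safety endpoint. SAEs are evaluated from D1 to D28 and go to the ethics committee within 24 hours, and mortality is an efficacy endpoint under intention to treat. What counts as an attempt may be settled in the full protocol.

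Much of this stands, and it narrows the group at risk. It does not remove the recording condition, which excludes patients on either reading. Nor does it settle the first condition, where the article's own usage points both ways.

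A reader might infer three stronger conclusions that the documents do not support:

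- *PTF harm is understated.* This needs excluded patients to have more events than included ones. That is plausible, but no rate is given. Tubes may also go uninserted in either arm, and nothing documents how rarely a nasogastric insertion is abandoned.
- *Early deaths as such leave the set.* Only deaths before placement (if that means a tube placed) or without recorded endpoints do.
- *The understatement is several-fold.* Assume 10% aborted, 60% of those with an event, and 2% among completed placements: 0.10 × 60% + 0.90 × 2% = 7.8%, or 3.9 times 2%. The 2% does not fit the MATE definition, which counts any fluctuation of HR, RR or MAP beyond 15% and the need for sedatives during placement, in an arm that is narcotized. With 10% the result is 6% + 9% = 15%, a factor of 1.5. With 20% it is 6% + 18% = 24%, a factor of 1.2.

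**Conclusion.** The point holds as a defect of definition. The adverse-event denominator depends on two post-randomisation conditions, at least one of which excludes patients on any reading, and both can be related to procedural harm. The procedures differ between arms, so PTF harm can be understated. Whether it will be, and by how much, cannot be computed from the documents. Under the assumed 5% excluded and 10% event rate among those included, the error runs from −4.5 to +0.5 points and is zero when included and excluded patients have the same rate. The denominator also conflicts with the statements that patients without a tube stay in the analyses and that all analyses follow intention to treat. Because safety is a primary objective and the correction is cheap, it should be made. It has no bearing on the sample size of 924.

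**What to change.** - Define the safety set as all randomised patients in whom feeding-tube placement was attempted (sedation for placement begun, or tube or endoscope introduced), whether or not a tube was left in place.
- Delete the condition that safety endpoints be recorded. Keep patients with an incomplete MATE assessment or an early death in the denominator, taking events from the SAE and death records.
- State the arm in which these patients are analysed, for example by the procedure first attempted, so that a rescue gastric tube does not move an event of the PTF procedure to the GTF arm.
- Reconcile Security set with Analyses set and Data analysis: either exempt the safety analyses from the general intention-to-treat sentence, or report the all-randomised result alongside.

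The cost is wording in these sections and one eCRF field for attempt started or aborted. No extra patients or procedures are needed. The reported PTF event rate may look slightly less favourable.

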#### Data analysis

All analyses will be performed according to the ITT principle. A *P* value < 0.05 is considered statistically significant. All tests are two-sided with no adjustment for multiple comparisons. Continuous variables are reported as means and standard deviations or medians and interquartile ranges. Categorical variables are reported as proportions. Pearson’s chi-squared test and adjusted multivariable analysis will be applied for the primary outcome. We plan to perform subgroup analyses for the primary outcome for predefined variables: the proportion of patients with at least 1 VAP episode. All the other data, including age, gender, body mass index (weight, height), SOFA score, primary admission diagnosis, coexisting illness, and type of admission, will be presented as descriptive results. Pearson’s chi-squared test will compare incidence or mortality outcomes between groups. The *t*-test will compare total VAP episodes, SOFA scores, time to VAP onset from mechanical ventilation, mechanical ventilation duration, ICU and hospital lengths of stay, inflammatory biomarkers, and function indicators between groups. A paired *t*-test or repeated measures ANOVA will be used to compare baseline and changes during the intervention.

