## Methods/design

### Study design

The VIP study is designed as a prospective, multicenter, open-label, randomized, parallel-group, GTF-controlled (PTF vs. GTF 1:1) superiority trial in 4 tertiary care hospitals. The participating sites in this study include medical/surgical, medical, surgical, or emergency ICUs (see Table 1 for details of participating centers). Patient enrollment is expected to last for up to 36 months. The end of the study is defined as the last follow-up of the last enrolled patient. The trial has been registered at chictr.org.cn (ChiCTR2100051593). We used the Standard Protocol Items: Recommendations for International Trials (SPIRIT) reporting guidelines [29], and the SPIRIT checklist is attached in the Supplementary appendixes.

**Table 1 Tab1:** Research settings and names of each ethics committee

Research setting	Ethics committee name	Hospital rank and location
Maoming People’s Hospital	Medical Ethics Committee of Maoming People’s Hospital	Tertiary, Maoming, Guangdong, China
Guangdong Provincial People’s Hospital	Medical Ethics Committee of Guangdong Provincial People’s Hospital	Tertiary, Guangzhou, Guangdong, China
General Hospital of Southern Theater Command	Medical Ethics Committee of General Hospital of Southern Theater Command	Tertiary, Guangzhou, Guangdong, China
Heyuan People’s Hospital	Medical Ethics Committee of Heyuan People’s Hospital	Tertiary, Heyuan, Guangdong, China

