### Assignment of interventions

#### Sequence generation for allocation

Following informed consent and confirmation of inclusion and exclusion criteria, participants on mechanical ventilation will be randomly assigned in a 1:1 ratio to receiving either PTF or GTF. Allocation sequences are generated by computer-generated random numbers using the R package *blockrand* [33]. Stratified block randomization is employed to avoid inter-group differences (study or control group) due to differences in the source of patients in different hospitals. Each participating center is served as a stratification factor, and then the subjects in each ICU are randomized into other blocks. The subjects will be consecutively assigned when entering the trial. To reduce the predictability of a random sequence, blocking details are provided in a separate document that is unavailable to those who enroll participants or assign interventions.

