### Outcome measurements

Participants will be evaluated clinically and through laboratory testing according to Table 2. The following data will be recorded: demographics, VAP diagnosis, concurrent medical conditions and comorbidities, inclusion and exclusion criteria, the severity of illness and organ dysfunction scores, vital signs and laboratory results, potential confounding co-interventions (life-sustaining therapies and use of sedatives or vasopressors), and outcomes (vital status at ICU and hospital discharge, day 28 and day 90, ICU and hospital length of stay).

**Table 2 Tab2:** Trial schedule of the VIP study

Timepoint	Baseline	^**a**^Interventions									Termination
	^b^D0	D1	D2, ^c^N1	D..., N...	D4	D5	D6	D7	D8, N7	D…	D28
Eligibility screening	**×**										
Informed consent obtaining	**×**										
Randomization	**×**										
Medical history collection	**×**										
Population data collection	**×**										
Baseline data collection	**×**										
Evaluation of major adverse tube-associated events (MATE)		**×**	**×**								
Evaluation of ^d^EN related adverse events			**×**	**×**	**×**	**×**	**×**	**×**	**×**	**×**	**×**
Evaluation of serious adverse events		**×**	**×**	**×**	**×**	**×**	**×**	**×**	**×**	**×**	**×**
VAP episode		**×**	**×**	**×**	**×**	**×**	**×**	**×**	**×**	**×**	**×**
Microorganisms causing VAP		**×**	**×**	**×**	**×**	**×**	**×**	**×**	**×**	**×**	**×**
Duration of mechanical ventilation		**×**	**×**	**×**	**×**	**×**	**×**	**×**	**×**	**×**	**×**
SOFA score		**×**	**×**	**×**	**×**	**×**	**×**	**×**	**×**	**×**	**×**
CPIS score		**×**	**×**	**×**	**×**	**×**	**×**	**×**	**×**	**×**	**×**
Serum albumin and C-reactive protein		**×**	**×**						**×**		
ICU-acquired infections (bloodstream, urinary tract, catheter-related, and other infections)		**×**	**×**	**×**	**×**	**×**	**×**	**×**	**×**	**×**	**×**
Day calorie target		**×**	**×**	**×**	**×**	**×**	**×**	**×**	**×**	**×**	
Day actual calorie		**×**	**×**	**×**	**×**	**×**	**×**	**×**	**×**	**×**	
Day calorie deficit		**×**	**×**	**×**	**×**	**×**	**×**	**×**			
Ventilator free		**×**	**×**	**×**	**×**	**×**	**×**	**×**	**×**	**×**	**×**
Transfer out of ICU		**×**	**×**	**×**	**×**	**×**	**×**	**×**	**×**	**×**	**×**
ICU survival		**×**	**×**	**×**	**×**	**×**	**×**	**×**	**×**	**×**	**×**
Discharge		**×**	**×**	**×**	**×**	**×**	**×**	**×**	**×**	**×**	**×**
Hospital survival		**×**	**×**	**×**	**×**	**×**	**×**	**×**	**×**	**×**	**×**

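### The primary outcome has two analyses with no stated order between them, and the one named test ignores the centre stratification of the randomisation

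*Protocol article*

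**What the plan says.** The Data analysis section assigns two methods to the primary outcome in one sentence: Pearson's "chi-squared test and adjusted multivariable analysis will be applied for the primary outcome". Neither is called primary, supportive or a sensitivity analysis. The threshold is a P value "< 0.05 is considered statistically significant", and "All tests are two-sided with no adjustment for multiple comparisons".

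Under Sequence generation for allocation, patients are "randomly assigned in a 1:1 ratio to receiving either PTF or GTF" by stratified blocks. "Each participating center is served as a stratification factor", and the reason given is to avoid group differences "due to differences in the source of patients in different hospitals". The Study design section describes a "superiority trial in 4 tertiary care hospitals". No sentence in the statistical section mentions centre.

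**The concern.** There are two separate matters, and the first weighs more.

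- **No deciding test.** The document fixes two analyses of one endpoint at one threshold. If one gives P = 0.04 and the other P = 0.06, it has no rule for whether the trial succeeded. In an open-label trial, that choice should be settled before outcome data are seen.
- **Analysis and randomisation do not match.** The trial stratifies by centre because it expects hospitals to differ. A pooled chi-squared test leaves the between-centre variation in its variance although stratification has already removed it from the comparison. If centre rates differ, the standard error is somewhat too large and the test is conservative.

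**Working it through.** **Inputs from the protocol article.** Total 924, control rate 33.7%, relative risk reduction 51.4% (Sample size estimation); 1:1 allocation within centre (Sequence generation for allocation); 4 centres (Study design); two-sided 0.05 (Data analysis). No centre-level VAP rates are given, so every set of centre rates below is an assumption.

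**The plan's own figure.** PTF rate = 0.337 × (1 − 0.514) = 0.1638; difference 0.1732. Taking superiority by the stated 10% margin at one-sided 0.05 and 80% power:

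n per arm = [0.337 × 0.663 + 0.1638 × 0.8362] × (1.645 + 0.842)² / (0.1732 − 0.10)² ≈ 416.

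The total is 832, and 832 / 0.9 = 924.4, which matches 924. Whether that basis fits the two-sided test in the Data analysis section is a separate question. Here 924 is used only as the trial size.

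**Step 1: two P values, success if either is below 0.05.** With both statistics standard normal under the null and correlation ρ, the probability that at least one exceeds 1.96 in absolute value is:

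| ρ | Type I error |
|---|---|
| 0.99 | 5.7% |
| 0.95 | 6.5% |
| 0.90 | 7.0% |
| 0.80 | 7.8% |
| 0 (independent) | 1 − 0.95² = 9.75% |

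If the adjusted analysis is only centre-stratified, 1:1 allocation within centre makes the pooled and stratified differences nearly identical, so the two tests differ only through the standard error. Simulation (200,000 replicates, 924 patients, 4 equal centres) gives 5.0-5.1% for either test rejecting.

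**Step 2: information lost by the unstratified test.** With equal centres and mean rate p̄:

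ratio = p̄(1 − p̄) / mean[pᵢ(1 − pᵢ)]; type I error = 2Φ(−1.96 × √ratio); information lost = 1 − 1/ratio.

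For assumed rates 20/30/40/45%:

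- p̄ = 33.75%, close to the stated 33.7%.
- p̄(1 − p̄) = 0.3375 × 0.6625 = 0.2236.
- Mean within-centre variance = (0.16 + 0.21 + 0.24 + 0.2475) / 4 = 0.2144.
- Ratio = 1.043.
- Type I error = 2Φ(−2.00) ≈ 4.5%.
- Information lost = 1 − 1/1.043 = 4.1%, or 924 × 0.041 ≈ 38 patients.

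**Step 3: simulated Pearson against the centre-stratified Cochran-Mantel-Haenszel (CMH) test.** Each row has mean control rate 33.7%.

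| Assumed control rates | Type I, Pearson / CMH | Power at assumed RR 0.75, Pearson / CMH |
|---|---|---|
| Equal | 5.1% / 5.0% | 80.5% / 80.4% |
| 25-43% | 4.8% / 5.0% | 80.6% / 80.9% |
| 10-60% | 3.4% / 5.0% | 82.0% / 85.3% |

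At the planned relative risk of 0.486, both tests have power above 99.9% in all three rows.

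**The case against.** **A natural order can be read in.** The unadjusted test could be the main comparison and the adjusted model supportive. The same section later gives incidence outcomes to the chi-squared test alone, which fits that reading. It is plausible, but it is not stated, and it would make the unstratified test the deciding one.

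**Covariates belong in an analysis plan that is not shown.** This stands. The unnamed model and covariates are no finding, and the adjusted analysis may well include centre. What remains is that the text itself fixes two tests without an order.

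**A reader might infer that the model will adjust for post-randomisation variables**, because the Outcome measurements section speaks of "potential confounding co-interventions (life-sustaining therapies and use of sedatives or vasopressors". The documents do not support this. The phrase stands in lists of data to be recorded, there and under Data management. No sentence puts these variables into the primary model.

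**A reader might infer a large loss of precision.** Assumed rates of 5/20/30/40% give a ratio of 1.102 (about 85 of 924 patients), and 5/5/40/40% give 1.213 (about 162). Those sets average 23.75% and 22.5%, well below the 33.7% control rate. They also borrow the 5 to 40% literature range in the Discussion, which that section attributes partly to differing diagnostic criteria. This trial uses one standardised definition with adjudicators unaware of allocation. The set used in Step 2 matches the control rate, although its top value of 45% also lies outside that range.

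**The unstratified test errs on the safe side.** This is true: it adds no false-positive risk, and its standard error is too large only if centre rates differ.

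**Conclusion.** The point holds in a limited form. The missing order between two primary analyses is the main part. The type I error from taking either result ranges from no real inflation (5.0-5.1%, adjustment for centre only) to about 5.7-7.0% at correlations of 0.99-0.90. The true correlation is unknown because the adjusted model is not described.

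The mismatch with stratification is a smaller matter of efficiency. It applies only if the Pearson test decides the trial and centre rates differ. Under the assumed 20/30/40/45% the cost is about 4% of the information and a type I error near 4.5%. At an assumed RR of 0.75 the simulated power cost is about 0.3 points for control rates of 25-43%, and about 3 points only for the wide 10-60% spread. At the planned effect it is immaterial. The result of the trial is not invalid on this account, but the gap can be closed at no cost.

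**What to change.** State one primary analysis: the ITT set, with a method that accounts for centre. An example is the centre-stratified Cochran-Mantel-Haenszel test, reported with a stratified risk difference or risk ratio and its 95% CI. State that this result alone decides the trial.

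Label as supportive the unstratified chi-squared test and any further adjusted model, and limit that model to baseline covariates. The Per protocol set section also applies that set to the primary endpoint, so say in the same sentence that this analysis is supportive too.

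The cost is wording in the protocol or analysis plan, settled before outcome data are compared by group. Sample size, data collection and trial conduct do not change, because centre is already recorded as the stratification factor.

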#### Secondary efficacy endpoints

The secondary efficacy endpoints of this trial include the following:Incidence analysis: including the cumulative VAP incidence and the total number of VAP episodes and numbers and percentages of microorganisms causing VAPMortality analysis: including ICU, hospital, and day-28 mortality ratesTime analysis: including time to VAP onset from mechanical ventilation, delayed time to first VAP occurrence, mechanical ventilation duration, the number of ventilator-free days until day 28, and ICU and hospital lengths of stayEnteral feeding and nutritional status: including the proportions of patients with at least one vomiting episode, prokinetic treatment, and diarrhea; the proportion of patients given 100% of the calorie target; cumulative calorie deficit from day 0 to day 7; and variations in serum albumin during the first week of enteral nutritionOrgan functioning: including score variations in Sequential Organ Failure Assessment (SOFA)Inflammatory level: including variations in serum C-reactive protein (CRP) levels during the first week of enteral nutritionICU-acquired infection: proportions of patients with ICU-acquired infections (bloodstream, urinary tract, catheter-related, and other infections); score variations in CPIS

We plan to collect data on organ dysfunction at baseline and at various time points during the study. All the six domains of the SOFA score, including respiratory, coagulation, hepatic, cardiovascular, renal, and central nervous system, will be documented. Vasopressors, sedatives, and renal replacement therapy will also be reported to assess organ dysfunction. VAP episodes are monitored during the whole study. New-onset VAP is diagnosed if new microbial culture results from distal respiratory specimens are different from those prior, and colonization is excluded.

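### Secondary change endpoints (SOFA, CPIS, CRP, albumin): no between-arm analysis named for them uses the baseline value, and CPIS and albumin have no clearly named between-arm test

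*Protocol article*

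**What the plan says.** The Secondary efficacy endpoints section of the protocol article defines four of its endpoints as changes: SOFA score, CPIS, serum CRP and serum albumin, the last two over the first week of enteral feeding. The Data analysis section has two sentences that bear on them.

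- **Between groups:** a t-test "will compare total VAP episodes, SOFA scores, time to VAP onset from mechanical ventilation", and, at the end of the same list, "inflammatory biomarkers, and function indicators between groups". CRP falls naturally under inflammatory biomarkers. CPIS and albumin are not named, and function indicators is not defined.
- **Change from baseline:** a paired t-test or "repeated measures ANOVA will be used to compare baseline and changes during the intervention". No variable is named, and neither a group factor nor a group-by-time term is mentioned.

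The only adjusted analysis is for VAP itself: "adjusted multivariable analysis will be applied for the primary outcome". On baseline data, the Secondary efficacy endpoints section says "We plan to collect data on organ dysfunction at baseline and at various time points during the study". The Data management section lists organ dysfunction scores and laboratory results among the baseline variables. Table 2 marks baseline data collection at D0. Randomisation is stratified by centre.

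**The concern.** The endpoints are changes, and the sentence written for changes leaves open two methods that answer different questions. A paired t-test compares patients with their own baseline and is silent on one feeding route against the other. Repeated measures ANOVA compares the arms only if it carries group and group-by-time terms, and the article does not say that it does. Even then it is not adjusted for baseline.

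Two things are at stake. One is precision: the trial collects a baseline value that usually predicts follow-up, and no method named for these endpoints uses it as a covariate. The other is interpretation. If paired tests are reported by arm, a reader may take significance in one arm only as evidence of a treatment effect. The article also states "All tests are two-sided with no adjustment for multiple comparisons", so nothing in the testing rules restrains such a reading.

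**Working it through.** The plan gives no figure for these endpoints, so there is none to reproduce. Three checks were made.

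**1. Precision.** Let r be the correlation between baseline and follow-up. The documents give no value, so r is an assumption, shown at 0.3, 0.5 and 0.7. Assume equal variance at both times, scaled to 1, and the same r in both arms. The variance of the treatment effect is then proportional to:

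- follow-up t-test: 1
- change-score t-test: 1 + 1 − 2r = 2(1 − r)
- ANCOVA: 1 − r²

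| r | Follow-up | Change score | ANCOVA | ANCOVA v follow-up | ANCOVA v change score |
|---|---|---|---|---|---|
| 0.3 | 1 | 1.40 | 0.91 | 9% lower | 0.91/1.40 = 0.65, 35% lower |
| 0.5 | 1 | 1.00 | 0.75 | 25% lower | 0.75/1.00 = 0.75, 25% lower |
| 0.7 | 1 | 0.60 | 0.51 | 49% lower | 0.51/0.60 = 0.85, 15% lower |

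ANCOVA has the smallest variance at every r shown.

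**2. Repeated measures ANOVA with a group factor.** In a simulated data set with two time points, the group-by-time F was 0.4337 and the squared two-sample t on the change was also 0.4337. With two time points, therefore, this model is a randomised comparison of change, and its precision is that of the change-score column above.

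**3. Paired tests read arm by arm.** Inputs: 924 patients at 1:1 gives 462 per arm, and the 10% loss allowed in the Sample size estimation section leaves 462 × 0.9 = 415.8, about 416. The test is two-sided at 0.05. Suppose the true change is the same in both arms, so that there is no treatment effect. If p is the power of the paired t-test in one arm, the chance that exactly one arm is significant is 2p(1 − p).

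| True change in each arm (SD of the change) | p | 2p(1 − p) |
|---|---|---|
| 0 | 0.050 | 9.5% |
| 0.05 | 0.174 | 28.8% |
| 0.10 | 0.530 | 49.8% |
| 0.15 | 0.863 | 23.7% |

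Within-arm tests therefore cannot stand in for the comparison of arms. The table shows what would happen if they were used that way; the article does not say that they will be.

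**The case against.** The strongest reply is that a randomised comparison is already planned. The sentence just before the one on change assigns a between-group t-test to SOFA scores and inflammatory biomarkers. With complete data that test is unbiased under randomisation, no power claim rests on these endpoints, and model terms and covariates are often left to an analysis plan that is not shown here. This largely stands. It limits the point to precision and clarity, but it does not supply a between-group test for CPIS and albumin. The article has also chosen methods for these endpoints, so a better choice is a fair comment.

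Three stronger readings are tempting, and the documents do not support them.

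- *The arms will be judged by contrasting within-arm p-values.* The article does not say this. The sentence on change does not say within arm and lists no variables, and repeated measures ANOVA can carry a group-by-time term.
- *Patients who die or leave the ICU will be dropped, against the statement* "All analyses will be performed according to the ITT principle". Paired t-tests need complete pairs and classical repeated measures ANOVA needs complete series, so loss is possible. No exclusion is stated, however, and the handling of missing serial values may be set out in the unseen analysis plan.
- *The albumin and CRP comparison is distorted by timing or lacks a baseline.* Table 2 first marks these two at D1, and the endpoints run from the start of enteral feeding. But D0 has a general baseline entry, laboratory results are listed as baseline variables, and nothing says that feeding starts at different times in the two arms.

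**Conclusion.** The point holds as a low-priority improvement confined to secondary endpoints. No baseline-adjusted between-arm analysis is named for SOFA, CPIS, CRP or albumin change. CPIS and albumin lack a clearly named between-arm test, unless function indicators is meant to cover them. The paired t-test cannot supply one.

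The variance reduction from ANCOVA is 9% to 49% against a follow-up t-test and 15% to 35% against a change-score test, for r between 0.3 and 0.7. These figures rest on the assumed r, on equal variances at the two times, and on complete data. The second gain is that readings based on significance in one arm only are avoided. The planned between-group t-tests on SOFA and inflammatory biomarkers are not biased by lack of adjustment, and the primary analysis is untouched.

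**What to change.** Replace the sentence on change with one between-arm analysis for each of SOFA, CPIS, CRP and albumin:

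- ANCOVA where there is a single follow-up value, with arm, baseline value and centre.
- A linear mixed model where values are serial, with arm, baseline value, centre, day and arm-by-day, using all available measurements.
- Paired within-arm tests kept for description only.
- A definition of function indicators, or its removal, and a statement of which measurement is the baseline for each endpoint. CPIS is not named in the list of baseline variables.
- Results reported beside mortality, with a statement of how scores are treated once a patient has died. A mixed model does not resolve truncation by death.

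The cost is analysis wording, with no extra patients and, where baseline values are already recorded, no extra measurements. Recruitment has begun, so a baseline that was not taken cannot be recovered for patients already enrolled; that should be checked first. The downside is that the mixed model assumes data missing at random for patients discharged early.
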